#### Secondary endpoints

The secondary clinical objectives are to examine changes on the cardiopulmonary exercise outputs (VO_2_max, anaerobic threshold, and peak workload) and echocardiographic measures; and to evaluate differences in the Scale for the Rating and assessment of Ataxia (SARA), modified Friedreich Ataxia Rating Scale (m-FARS), 9-hole pegboard test (9HPT), EQ-5D, Activities of Daily Living (ADL)/Instrumental Activities of Daily Living Scale (IADL), and number and distribution of serious and non-serious adverse events between DMF and placebo.

The secondary laboratory objectives are to determine the effect of DMF on *FXN* and frataxin protein considering the change from baseline to week 12 and week 24 and at week 1 of the core phase, and at week 1 of the extension phase for those patients transitioning from placebo to DMF, compared to other time-points obtained after a DMF dose of 240 mg BID. Other secondary endpoints explore the effect of DMF on Nrf2 pathway genes (*NFE2L2, NQO1, HMOX1, PDLIM1*, and *NCF2*), on mitochondrial biogenesis genes (mt-ND6, mtCYB, mt-CO_2_, and mt-ATP6), and on mtDNA/nDNA.

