### Sample size calculation

Sample size calculation was performed based on our preliminary results of DMF treatment in patients with Multiple Sclerosis and is based on the estimated increase in FXN expression with the following assumptions derived from our preliminary data (Jasoliya et al., 2019). We previously found a significant +85% increase in the group treated with DMF compared to no increase in the control group (time^*^treatment interaction *p* = 0.02), which resulted in a partial eta square of 0.198. The sample size in this study was 14 patients treated with DMF and 13 with reference control treatment. The partial eta square of 0.198 results in an effect size of 0.497. Estimating the effect size based on preliminary data on MS patients is an underestimation of the potential effect of DMF in FRDA patients. Indeed, DMF can overexpress FXN through two mechanisms. One is the stimulation of nrf2 and the increase in transcription of several genes, including antioxidant genes and frataxin. This mechanism is clearly involved in MS patients treated with DMF. The second mechanism is the ability of DMF to induce transcription initiation and reduce transcriptional pausing in mutant *FXN* gene. This mechanism is unique to FRDA patients as it requires a mutated gene to be effective. In support of this, experiments in patients' lymphoblasts treated with DMF have found up to a +260% increase relative to baseline (Lynch et al., 2010), compared to our finding of +85% increase in MS patients treated with DMF. Based on this data, we calculated the appropriate sample size for this study using G^*^Power version 3.1.9.6. We used an ANOVA for repeated measures, within-between interaction, as the appropriate test. Effect size was set at 0.497, alpha error at 0.05, power at 0.8, number of groups 2, number of measurements 2, and non-sphericity correction 1. This results in a total population of 36 patients (18 treated + 18 placebo). We will prudently include 40 patients in total, allowing us to compensate for a lost at follow-up of up to 10% of randomized patients.

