### Statistical analysis

All data will be preliminary tested for normality using the Kolmogorov–Smirnov test. Since quantitative real time PCR (qPCR) data are frequently not normal, a normalization attempt, using ln or log transformation, will be performed. qPCR data will be calculated as relative increases imputing a baseline expression level of 1.0. Main statistical analysis of both FXN expression and frataxin protein level will be conducted with a Generalized Linear Model (GLM) for repeated measures. GLM incorporates a two-way ANOVA for repeated measures and can accommodate a multivariate analysis of factors and covariates. Treatment with DMF or placebo will be considered as a factor, and baseline levels of frataxin will be considered as a covariate. FXN baseline expression will not be used in the model as it is already integrated using relative expression with common baseline. All other available data (sex, age, disease duration, GAA1, and treatment specific findings, etc.) will be preliminarily tested one by one as covariates. In case of resulting *p*-values < 0.1, they will be integrated in the final multivariate model with treatment as a factor. In case of a significant Maulchy's sphericity test, we will use the Greenhouse-Geisser correction. We will use a similar analysis approach for remaining secondary endpoints. This will include different time-points from FXN and frataxin, and other qPCR analysis, SARA, 9HPT, PRT, ADL/IADL, and EQ-5DVAS. The main analysis will be conducted with results from the core phase of the trial (20 patients treated with DMF and 20 with placebo) and will be used to draw conclusions on the efficacy of DMF. A secondary analysis will be conducted adding to the model patients from the extension phase that switched from placebo to DMF (total of 40 DMF vs. 20 placebo). This analysis will be considered as descriptive and not used to drive efficacy conclusions. For adverse events (AEs), we will perform a descriptive analysis of AEs including their distribution in DMF and placebo treated patients, AEs duration, severity, and connection to the study drug. To test if treatment with DMF increases the likelihood of having an AE, we will use a Generalized Linear Model with Poisson distribution and treatment as a factor. To test if a single AE is more frequently linked to DMF treatment, we will use the exact test of Goodness of fit, assuming an equal proportion of adverse events in the treatment and placebo group. This will be possible only for adverse events occurring at least once in both groups. For baseline variables a descriptive analysis will be performed, and difference between DMF and placebo patients will be tested with an unpaired *t*-test and chi-square test, depending on the variable. In case of non-normal distribution, a Mann–Whitney test will be used in place of a *t*-test. A two-sided significance level of 5% will be required to reject the null hypothesis that the outcome measures are the same before and after treatment, and for all other comparisons. The Bonferroni correction for multiple analyses will be used. Considering the primary endpoint and the phase of the trial, the analysis will be per protocol. Data will be analyzed using the SPSS 23 for MAC (IBM, Chicago, USA).

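### The plan's Bonferroni correction is valid, but Holm's step-down procedure gives the same family-wise error control and never rejects less, so it is a nearly free improvement of modest, family-dependent size.

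*Protocol article*

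**What the plan says.** In the Statistical analysis section, the protocol article sets the level: "A two-sided significance level of 5% will be required to reject the null hypothesis". The same sentence extends this level beyond the outcome measures to every other comparison. The next sentence is the whole multiplicity rule: "The Bonferroni correction for multiple analyses will be used". It does not say which tests form the family, how many there are, or whether the correction covers only secondary endpoints. It does not call the rule single-step, although that is the ordinary meaning of the name.

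The Secondary endpoints section lists many candidates for such a family. It introduces the mechanistic markers with "Other secondary endpoints explore the effect of DMF on Nrf2 pathway genes" and names five of these genes, four mitochondrial biogenesis genes and the mtDNA/nDNA ratio. Frataxin protein, three exercise-test outputs, echocardiographic measures and several clinical scales are also listed.

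The Sample size calculation section concerns FXN expression only: "Effect size was set at 0.497, alpha error at 0.05, power at 0.8, number of groups 2, number of measurements 2, and non-sphericity correction 1". No power is claimed for any secondary endpoint.

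**The concern.** Bonferroni compares every p-value in a family of m tests with 0.05/m. Holm uses that threshold only for the smallest p-value and relaxes it after each rejection. Both hold the family-wise error at 5% under any correlation, so where Bonferroni is used, Holm is available at no cost in error control.

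The difference matters most when many endpoints respond together. The Study rationale gives some reason to expect this: in patients with multiple sclerosis treated with DMF, all four mitochondrial transcripts and mitochondrial copy number rose. With about 18 evaluable patients per arm, power for these secondary comparisons is limited under any strict correction, so even a few percentage points are worth having if they cost nothing.

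**Working it through.** **1. Inputs from the article.** Two-sided alpha 0.05; 36 evaluable patients, 18 per arm; partial eta squared 0.198 (Sample size calculation).

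**2. The plan's own figure.** f = sqrt(0.198 / 0.802) = 0.497, as stated. With noncentrality f² × (N − 2) = 0.2469 × 34 = 8.39 and an F test on 1 and 34 degrees of freedom, power at N = 36 is 80.4%. At N = 34 it is 77.8%. The stated 36 is therefore reproduced.

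**3. Effect size for the comparison.** For two groups d = 2f = 0.994, rounded here to 1.0. Under the noncentrality in step 2, d = sqrt(8.39) / sqrt(18/2) = 2.897 / 3 = 0.966. Results for both follow. Applying this effect to secondary endpoints is an assumption, because the article derives it for FXN expression only.

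**4. Size of the family (assumed).** Five Nrf2-pathway genes + four mitochondrial genes + mtDNA/nDNA = 10. Adding frataxin protein (1), exercise-test outputs (3), SARA, m-FARS, 9HPT, EQ-5D, ADL and IADL (6) gives 20, before echocardiography and further time-points. I used m = 10 and m = 20.

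**5. The two rules.**
- Bonferroni: reject if p ≤ 0.05/m.
- Holm: order the p-values; reject the i-th smallest while p(i) ≤ 0.05/(m − i + 1), and stop at the first failure.

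For m = 10 the Bonferroni threshold is 0.005 throughout. The Holm thresholds rise: 0.005, 0.0056, 0.0063, 0.0071, 0.0083, 0.010, 0.0125, 0.0167, 0.025, 0.05. No Holm threshold is below 0.05/m, so every Bonferroni rejection is also a Holm rejection. The first threshold is the same, so the chance of at least one rejection is identical.

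**6. Simulation.** Two-sample t tests on 34 degrees of freedom, 18 per arm, pairwise correlation 0.5 (assumed), 20,000 runs per row at d = 1.0 and 40,000 at d = 0.966. Entries are average power per responding endpoint, Bonferroni vs Holm.

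| Family m | Responding | d = 1.0 | Gain (points) | d = 0.966 |
|---|---|---|---|---|
| 10 | 1 | 50.9% vs 51.0% | practically 0 | 46.9% vs 46.9% |
| 10 | 3 | 50.7% vs 52.3% | 1.6 | 47.1% vs 48.8% |
| 10 | 5 | 50.7% vs 54.4% | 3.7 | 47.1% vs 50.5% |
| 10 | 10 | 50.7% vs 63.1% | 12.4 | 46.9% vs 58.9% |
| 20 | 5 | 41.3% vs 42.7% | 1.3 | 37.3% vs 38.5% |
| 20 | 10 | 41.2% vs 44.5% | 3.4 | 37.6% vs 40.7% |
| 20 | 20 | 41.0% vs 52.8% | 11.8 | 37.5% vs 48.3% |

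In the d = 1.0 runs no Bonferroni rejection was missed by Holm, and family-wise error was at most 3.6% for Bonferroni and 3.8% for Holm.

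**7. Sensitivity.** With effects half as large (same correlation), the gain is 0.5 points for 5 of 10, 1.5 for 10 of 10 and 0.3 for 10 of 20.

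**8. What Holm does not recover.** At d = 0.966 a single test has 80.4% power unadjusted, about 47% under Bonferroni with m = 10 and 37.5% with m = 20. Most of that fall comes from adjusting for many tests at all.

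**The case against.** The strongest reply is that nothing here is wrong. Bonferroni is a valid correction, no other statement in the article conflicts with it, the trial has one primary endpoint, and no power target is set for the secondary endpoints. All of that stands.

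A reader might infer from the ten molecular markers that Bonferroni discards a large share of their power. If exactly those ten formed the family and all responded at d = 1.0, the chance of confirming all ten would be 8% under Bonferroni and 37% under Holm. The article does not support that as the expected case. Its patient data cover five of the ten (four transcripts and copy number), and come from multiple sclerosis. NCF2 and PDLIM1 are supported only by lymphoblast lines. Nothing limits the family to ten. If all ten respond within a family of 20, confirming all ten changes from about 5% to 8%.

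A reader might also take the correction to concern secondary endpoints only. The sentence refers to multiple analyses and follows one covering all other comparisons. A replacement that names only secondary endpoints would change the scope of the correction without saying so.

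One part of the reply does not stand: that the choice is a matter of taste. For hypothesis tests, Holm is at least as good in every configuration and needs nothing extra.

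**Conclusion.** The point holds as an efficiency improvement. The plan names a valid procedure that another dominates uniformly at the same error rate. Per responding endpoint, the gain is practically zero with one responder, about 1 to 4 points with a quarter to a half responding, and about 12 points only if all respond. The chance of finding at least one effect is the same under both rules.

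These figures rest on 18 per arm, correlation 0.5, families of 10 or 20, and the FXN effect size carried over to other endpoints. All but the first are assumptions, and smaller effects shrink the gain. The dominance itself depends on none of them.

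The documents do not support calling this an error, a loss of promised power or a threat to the primary conclusion. The undefined family is a separate matter that Holm does not settle. If the primary test were counted in the family, Bonferroni would take its power at N = 36 from 80.4% to 70.8% with two tests and to 46.9% with ten.

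**What to change.** In the Statistical analysis section, replace the Bonferroni sentence with:

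*Wherever the Bonferroni correction for multiple analyses would apply, the Holm step-down procedure will be used at a two-sided family-wise level of 5%, and Holm-adjusted p-values will be reported.*

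This keeps the scope of the correction as the plan has it. The adjusted p-values come from sorting the p-values already planned: the i-th is the largest value of min(1, (m − j + 1) × p(j)) over j ≤ i. No further patients, data or assumptions are needed. The one downside is that simultaneous confidence intervals matching Holm are less simple than Bonferroni intervals; the Statistical analysis section mentions none. The change should be made before unblinding.

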
### Good clinical practice

Physicians will perform the study in accordance with ICH Good Clinical Practice and Good Clinical Practice for Trials on Medicinal Products in the European Community (ISBN 92-825-9563-3). The Investigator is required to ensure his/her compliance to procedures required by the protocol. The Investigator agrees to provide all information requested in Case Report Form in an accurate manner. The Investigator is required by Italian Health Authorities to ensure the proper conduct of the study as regards ethics, protocol adherence, integrity, and validity of the data recorded on the case report forms. Specific hazards for this study are the respect of inclusion and exclusion criteria. It is critical that all patients are correctly diagnosed with a molecular test and that this is available as a documentation of the study. Not allowed medications are another critical point as they could interfere with the study drug. This will be accurately checked by the study monitor before patients receive their first treatment. It is also critical that patients comply with the drug dose regimen, and this will be checked through compliance pill counts, house diaries, and drug accountability logs. Monitors will be required to check all of these procedures at each visit. Data generated during the study, and that will be collected in the eCRF, will be laboratory results, clinical scales, self-reported scales, concomitant treatment, and adverse events. All will be monitored at each visit for 100% coverage of all imputed data. A total of six monitoring visits will be performed during the study.

Compliance with the study protocol and risk minimization will be achieved through training of all site personnel at the beginning of the study and with periodical (every 3 months) meetings with update on enrollment, side effects, monitoring findings, DMF new SUSARs, and adherence to the programmed schedule. Meeting outcomes will be shared with the study personnel and with the study monitor.

## Discussion

The present trial is of extreme interest for healthcare providers as no approved therapy for FRDA exists in Europe. This results in the use of symptomatic therapy for the treatment of cardiac and orthopedic complications, diabetes, depression, and urinary disturbances, and in the chronic support through physiotherapy.

Recently, Omaveloxolone has been approved in the US by the FDA to treat FRDA patients. Despite a pending approval from EMA, there is still a need for multiple therapeutic choices for the disease, for improved disease modifying effect, and for more robust effects on the primary molecular defect (i.e., low frataxin expression).

Current therapies cannot halt disease progression, which occurs over time. Onset occurs usually when patients are in their teenage years and causes patients to be wheelchair-bound ~10 years after diagnosis. The result is that the social costs for such disability are both direct, for the costs of physiotherapy and symptomatic drug management, but also indirect for their loss in productivity. The availability of an effective treatment able to halt or slow disease progression may be of immense value as it may help reduce both healthcare and social costs of the disease.

## Ethics statement

The studies involving humans were approved by the Clinical Trial Information System (CTIS) with the ID number 3873. The studies were conducted in accordance with the local legislation and institutional requirements. The participants provided their written informed consent to participate in this study.
